## Interventions

### Explanation for the choice of comparators {6b}

The control intervention is the most frequently used dose and considered international standard of care for systemic therapy of ISSHL (e.g., [26, 28, 32, 40]). According to the Declaration of Helsinki and to clinical experience, a placebo control is not acceptable and not feasible with respect to the patient’s expectance of treatment and ethical considerations. In Germany, a high-dose glucocorticoid therapy (250 mg prednisolone or equivalent glucocorticoid dose) is suggested in the German ISSHL guideline [3] without its effectiveness being proven in an RCT. Niedermeyer et al. (2003) showed in humans that inner ear cortisol levels were only increased after 250 mg of prednisolone (i.v.) but not after 125 mg (i.v.) [25]. The rationale for using a second, high-dose glucocorticoid treatment arm is based on the report of Egli Gallo et al. (2013), who retrospectively evaluated the effectiveness of systemic high-dose dexamethasone therapy (administered orally) and demonstrated a significantly better improvement of hearing compared with a historical control using the clinic’s earlier treatment regimen (standard prednisone [11]). Oral therapy would increase feasibility of the treatment for the patient compared with daily i.v. application and thus also demonstrates a patient-relevant outcome if shown to be effective.

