### Sample size {14}

This three-armed trial (randomization ratio: 1:1:1) is aimed at comparing standard-dose systemic therapy with two types of high doses of systemic therapy concerning the primary endpoint using two individual statistical tests assuming a normal distribution of the primary endpoint in the population. For a global significance level of 0.05, we adjust for two tests using a local level for each test of 0.025. The following assumptions are based on the available literature [32]. A sample size of 88 in each group will have 80% power to detect a difference between high dose and standard dose, when the true difference in means is −10.0 (e.g., the difference between a group 1 mean, μ1, of 30.7 and a group 2 mean, μ2, of 40.7) assuming that the common standard deviation is 21.3. The sample size calculation was performed for two-sample *t* tests with nQuery Version 7.0. Assuming a dropout rate of approximately 15%, a total of 312 patients need to be randomized (1:1:1) to maintain at least 264 evaluable patients with complete data (high-dose dexamethasone: 104; high-dose prednisolone: 104, standard prednisolone: 104).

Systemic glucocorticoids are the standard treatment in ISSHL. Since the study drugs thus do not involve a completely new therapeutic concept, patient compliance is generally estimated as high. We assume a rate of loss to follow-up of 15%. This estimate is based on two recent RCTs on ISSHL. Nosrati-Zarenoe and Hultrantz (2012) randomized 103 patients and were able to analyze 88 (85%) on day 8 of the assessment and 73 (71%) at the 3‑month time point [26]. In the study of Rauch et al. (2011), 221 of 255 patients (87%) completed the intervention and 2‑month follow-up (per-protocol analysis [32]).

The trial will be analyzed according to the intention-to-treat principle including all randomized patients. A per-protocol analysis will be performed as sensitivity analysis.

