## Statistical methods

### Statistical methods for primary and secondary outcomes {20a}

The primary confirmatory analyses will be based on the intention-to-treat population (ITT), which will include all randomized patients. The analysis will be done according to the intention-to-treat principle; this means every patient remains in the treatment group as allocated by randomization. The per-protocol population (PP) will be formed from the ITT. Only patients with major protocol violations will be excluded. The details will be described in the final statistical analysis plan.

The PP will be the secondary analysis population for PP analysis to confirm the results of the ITT analysis.

The confirmatory analysis of the primary endpoint is planned after complete documentation and data cleaning including visit 9. The confirmatory analysis aims on showing the superiority of one or both of the high-dose treatments in comparison with the standard therapy. Therefore, two analyses of covariance (adjusted for baseline PTA) will be performed at a local significance level of α = 0.025 (two sided), which means for a global significance level of α = 0.05 (two sided) for the statistical evaluation of the primary endpoint.

The differences in the primary endpoint between the high-dose groups and the standard group will be estimated with 97.5% confidence intervals (being confirmatory and consistent to the test procedure) and with 95% confidence intervals (being comparable to results usually presented in the literature).

The sample size of the study was planned to achieve a high power for the comparisons of high dose vs. standard dose. But, if superiority of both high-dose treatments versus the standard treatment can be shown, both high-dose treatment arms will be compared at a significance level of α = 0.05 (two sided) and the difference will be estimated with 95% confidence interval as a secondary objective.

The data of the ITT and PP will be statistically described in detail. This includes:Listings of all documented data for every patient.Summary tables of all variables. Discrete variables will be described by absolute and relative frequencies. Continuous variables will be described by statistical characteristics (minimum, maximum, quartiles, median, mean, standard deviation).

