The secondary endpoints will be analyzed as follows:Speech discrimination using Mann–Whitney tests as these values are usually not normally distributed.Comparison of patients with complete, partial, or no improvement will be compared with a Cochrane–Armitage test for trend.Data from QoL questionnaires using chi-squared tests and Mann–Whitney tests as adequate.

All statistical tests in connection to the secondary endpoints will be performed for descriptive purposes. The *p *values will be given without adjustment for multiple testing.

To evaluate the role of the baseline PTA as a prognostic or predictive factor for the primary and secondary endpoints, it is planned to analyze two subgroups according to baseline hearing loss (< 81 dB vs. ≥ 81 dB). The analysis will be the same as that for the primary intention-to-treat analysis including a test for interaction of baseline hearing loss and therapy.

Safety analyses will be performed in the safety population including all patients for whom one of the randomized treatments was started. Here, patients will be analyzed according to treatment received. Rates of adverse events and of serious adverse events will be calculated.

All confirmatory analyses were fully specified in the trial protocol. Other details of the statistical analysis will be fixed at the latest in the Statistical Analysis Plan, to be prepared during blind review before database lock.

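### The estimate, and not only the test, of high-dose prednisolone versus high-dose dexamethasone is planned only for the case where both arms beat standard

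*Protocol article*

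**What the plan says.** The protocol article describes a three-arm superiority trial. Each high-dose arm is compared with standard-dose prednisolone on the change in pure tone average at 30 days. The section Sample size {14} sets the error rates: "For a global significance level of 0.05, we adjust for two tests using a local level for each test of 0.025". The section Statistical methods for primary and secondary outcomes {20a} carries this out with two ANCOVAs adjusted for baseline PTA, each two-sided at 0.025. Superiority of one or both high-dose arms meets the confirmatory aim. Each arm's difference from standard is given with 97.5% and 95% confidence intervals whatever the tests show.

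The comparison between the two high-dose arms is treated differently. The section says that "if superiority of both high-dose treatments versus the standard treatment can be shown, both high-dose treatment arms will be compared at a significance level" of 0.05 two-sided. The same sentence adds the 95% confidence interval for the difference and calls the comparison a secondary objective. No between-regimen test or estimate is described for the case where only one arm, or neither, beats standard.

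On why there are two high-dose arms, the section Explanation for the choice of comparators {6b} cites first a retrospective report of better hearing with oral dexamethasone. It then adds a practical point: "Oral therapy would increase feasibility of the treatment for the patient compared with daily i.v. application".

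**The concern.** A test and an estimate need different protection. A hierarchical gate keeps a further significance test from inflating the error rate after the two primary tests have used the full 0.05. A confidence interval labelled as descriptive uses no alpha and needs no gate. By putting both behind one condition, the plan drops the estimate for no statistical gain.

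The loss matters most when exactly one arm beats standard. The plan counts that as success, so it is a foreseen outcome. The report would then show one regimen significant and the other not, without the adjusted difference and interval that tell a reader whether the two regimens can be separated at all. With two equally good regimens, such a split is mostly chance.

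There is also a selection effect. If the regimens truly differ, both tend to win in trials where the weaker arm happened to do well. A difference reported only in those trials is too small on average.

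**Working it through.** **Inputs, all from Sample size {14}.** The planned power is stated as follows: "A sample size of 88 in each group will have 80% power to detect a difference between high dose and standard dose". The assumed gain is 10 dB and the SD 21.3 dB in every arm. The local level is 0.025, which section 20a states is two-sided; allocation is 1:1:1 and dropout about 15%.

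**Step 1: reproduce the plan's figure.** Write the gain as a positive number.

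- SE of a difference between two arms = 21.3 × √(2/88) = 3.21 dB.
- Noncentrality = 10 / 3.21 = 3.11. The critical t (174 df, two-sided 0.025) is 2.26.
- Power is 80.2% at n = 88 and 79.7% at n = 87, so 88 is right.
- 88 / 0.85 = 103.5, rounded up to 104; 3 × 104 = 312. This also agrees.

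**Step 2: how often the gate stays shut.** The two primary contrasts share the control arm, so their estimates have correlation 0.5. Simulation of 2,000,000 three-arm trials, 88 per arm, SD 21.3, two-sample t tests at two-sided 0.025, no precision gain from ANCOVA:

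| True gains (dB) | Both win | Exactly one | Neither | No between-regimen estimate |
|---|---|---|---|---|
| 10 and 10 (plan) | 69% | 22% | 9% | 31% |
| 8 and 8 (assumed) | 43% | 32% | 25% | 57% |
| 7 and 7 (assumed) | 30% | 33% | 36% | 70% |

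The last column is 100% minus the second. As a check on the first row, unrounded: 69.0% + 22.4%/2 = 80.2%, the single-test power from step 1. Only the 10 dB row uses a plan figure.

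**Step 3: what a split result means when the regimens are equal.** In the 10 and 10 dB trials with exactly one winner, the median observed gap between the regimens is about 3.7 dB. A direct two-sided test at 0.05 would be significant in about 14% of them (12% at 8 and 8 dB). Every such result is a false positive, because the true difference is zero.

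**Step 4: precision of the estimate that is dropped.** Half-width of the 95% interval = 1.97 × 3.21 = 6.3 dB. With equal arms this equals the 95% half-width for each primary contrast, so the comparison is not estimated less precisely than the primary ones.

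**Step 5: effect of reporting only after both win.** The true gains here are assumptions.

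| True gains (dB) | True difference | Gate opens | Mean difference when reported |
|---|---|---|---|
| 10 and 7 | 3 | 43% | 2.0 |
| 10 and 5 | 5 | 23% | 3.2 |

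An estimate reported in every trial has no such shrinkage.

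**The case against.** A reader might infer that the trial will single out one regimen because its p-value crossed the line and the other's did not. The documents do not support that. No section selects or ranks a regimen on significance. The Objectives section asks about high dose versus standard of care, and an arm that wins alone validly shows superiority to standard at 0.025. The risk lies in how a split result may be read, not in a rule of the plan.

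Several further points stand:

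- Gating the test is an accepted hierarchical procedure. Section 20a explains that the sample size was planned for high dose versus standard.
- A reader is not left with p-values alone. Each arm's difference from standard is reported with intervals, and means and SDs are tabulated, so a crude between-regimen difference can be worked out. The baseline-adjusted difference with its interval cannot.
- The main rationale for the dexamethasone arm is the retrospective efficacy report. Oral convenience is an added remark that applies if the regimen proves effective, so the choice between regimens is not a primary question.
- The statement that "All statistical tests in connection to the secondary endpoints will be performed for descriptive purposes" covers secondary endpoints such as speech discrimination. It does not govern a secondary comparison on the primary endpoint, so the gate does not contradict it.
- The 22% is the chance of discordant tests, not of a wrong claim. Any precision gained from the baseline covariate would lower it at 10 dB.

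The objection that this belongs to the SAP stands only in part. The SAP is not shown and could add a descriptive estimate, and the protocol does not forbid one. But the protocol does more than stay silent: it states when the difference will be estimated, and an SAP that follows it literally would leave the estimate out whenever the gate is shut.

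**Conclusion.** The point holds as a minor one. The testing procedure is sound and the familywise level is kept at 0.05. The weakness is that a named secondary objective is estimated only when both arms beat standard. Under the plan's own assumptions that leaves it unestimated in about 31% of trials, including the 22% with a split result. When the regimens truly differ, the conditional estimate is also too small on average.

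These figures assume 88 evaluable patients per arm, a common SD of 21.3 dB, normal outcomes, unadjusted t tests and, for the 31% and 22%, a true gain of 10 dB in both arms. The shrinkage figures rest on assumed unequal gains that the protocol does not give.

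**What to change.** In section 20a, and in the SAP, which the Trial status section describes as still being finalised before unblinding:

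1. Always report the prednisolone-minus-dexamethasone difference in the primary endpoint, adjusted for baseline PTA, with a 95% confidence interval. Label it descriptive when the gate is not met.
2. Keep the condition that both arms are superior for the significance test at 0.05 only.
3. State that superiority of one high-dose arm over standard is not by itself evidence that it is better than the other high-dose arm.

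The cost is two or three sentences and one descriptive line in the results table. No patients and no alpha are needed, and the familywise error of the two primary tests is unchanged.

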### Interim analyses {21b}

An interim analysis for the primary and secondary outcomes is not planned.

### Methods for additional analyses (e.g., subgroup analyses) {20b}

To evaluate the role of the baseline PTA as a prognostic or predictive factor for the primary and secondary endpoints, it is planned to analyze two subgroups according to baseline hearing loss (< 81 dB vs. ≥ 81 dB). The analysis will be the same as that for the primary intention-to-treat analysis including a test for interaction of baseline hearing loss and therapy.

### Methods in analysis to handle protocol non-adherence and any statistical methods to handle missing data {20c}

The influence of missing audiological data on the results of the final analysis will be evaluated in a blind review of the structure of missing data and the reasons for missing data. Centers with more than 30% missing data at visit 9 will be suspended as recruiting center. The handling of missing data in the final analysis will be determined in the statistical analysis plan and will depend on the analysis of the structure of the missing data. We expect that the organizational structure of the trial will produce a missing-at-random structure. In this case, multiple imputation methods can be used to insert missing data for the analysis. In addition, sensitivity analysis will be carried out to evaluate the influence of missing data.

### Plans to give access to the full protocol, participant level-data, and statistical code {31c}

According to the recommendations on data sharing by the International Committee of Medical Journal Editors (ICMJE), data resulting from the study will be made available to the scientific community as follows:

After publication of the major results and upon reasonable request from researchers performing an individual patient data meta-analysis, individual patient data that underlie published results will be shared after de-identification.

Summary statistics that go beyond the scope of published material will be made available to researchers for meta-analysis upon reasonable request and if the necessary data analysis is not unduly time-consuming. Together with publication of the main results, the study protocol in full will be made publicly available as well as the statistical analysis plan.

## Oversight and monitoring

### Composition of the coordinating center and trial steering committee {5d}

Study coordination, data management, monitoring, and safety management are done by the Coordination Center for Clinical Trials at University Medicine Halle (KKS Halle), which has comprehensive experience with managing drug trials. Tasks assigned to KKS Halle will be performed according to written standard operating procedures (SOPs).

### Composition of the data monitoring committee, its role, and reporting structure {21a}

To provide expert advice and independent trial monitoring, a Data and Safety Monitoring Board (DSMB or data monitoring committee, DMC) is established. The DSMB follows the progress of the clinical trial, evaluates the safety parameters, and proposes to the sponsor whether to continue, modify, or stop a trial. Prior to inclusion of the first patient, a DSMB charter will be established by specifying roles and responsibilities as well as meeting frequency and reviewed data. The DSMB sets up conference calls twice a year to evaluate current safety data. Therefore, the sponsor will provide up-to-date safety data including a summary of adverse events and line listing of serious adverse events. The DSMB will inform the sponsor about their recommendation for trial continuation/discontinuation. In the case of a high number of severe unexpected events in between DSMB meetings or a case of a suspected unexpected serious adverse reaction (SUSAR) or other medically important conditions, the DSMB will be informed by the sponsor immediately and may give advice for further procedures if required.

### Adverse event reporting and harms {22}

Clinical safety management will be performed according to ICH E2A guideline. Adverse events are to be reported in the CRF. Reporting of serious adverse events will follow guidance ENTR/CT 3 (Detailed guidance on the collection, verification and presentation of adverse reaction reports arising from clinical trials on medicinal products for human use). All adverse events occurring within 26 days of the initial administration of study medication (visit 8 = days 26–34) are to be documented as adverse events. If an adverse event meets one of the seriousness criteria, additionally expedited reporting to the sponsor applies. Sites are provided with a detailed safety manual. The sponsor reports safety issues further according to protocol and national laws. Safety analyses will be performed in the safety population including all patients for whom one of the randomized treatments was started. Here, patients will be analyzed according to treatment received. Rates of adverse events and of serious adverse events will be calculated.

### Frequency and plans for auditing trial conduct {23}

As a measure of quality control, risk-adapted on-site data monitoring is conducted during the enrolment period by independent clinical monitors from the KKS Halle and the ZKS Freiburg (Clinical Trials Unit of the Medical Center—University of Freiburg) to ensure patient safety, adherence to protocol and GCP, and consistency of the data. This is done according to GCP and SOPs. The specific extent of the monitoring and source data verification is specified in the monitoring manual. Every trial site will undergo a close-out visit by the monitors after the last participant at that site has finished the follow-up visit. In compliance with GCP guidelines, further audits may be performed as a quality measure by the sponsor or an independent external party, as well as inspections by regulatory authorities. To date, one of the trial sites and the KKS Halle have been inspected by responsible governmental authorities.

### Plans for communicating important protocol amendments to relevant parties (e.g., trial participants, ethical committees) {25}

Any protocol modifications are communicated to relevant parties including investigators and regulators. Substantial amendments that require approval according to the national GCP regulation (GCP‑V §10) will be submitted to the responsible ethics committee and the relevant federal authority for evaluation and are only implemented after their approval.

## Dissemination plans {31a}

The trial was registered with full description at the German Clinical Trials Register (*Deutsches Register Klinischer Studien*, DRKS). The results will be published independent of the size or direction of the effects, according to CONSORT guidelines, in peer-reviewed national and international journals with a special emphasis on media that is relevant for professionals in otorhinolaryngology. Beyond regular journal publication, results will be presented and discussed at national and international congresses addressing ENT specialists and specialists for internal medicine. Furthermore, the resulting evidence may be implemented into the German (and other) ISSHL guideline(s). Additionally, clinical trial summary results will be published in the European Union Clinical Trials Database (EudraCT). Relevant raw data will be made available in a data repository. Study results will also be published in the respective publications of patient self-help organizations. To enhance patient interest and support, we will provide information in lay language via specific publications on our homepages, printed flyers, and regular oral presentations at local and national meetings of patient organizations in Germany. Moreover, we will be in direct contact and interaction with healthcare providers and regulatory governmental authorities to support their decision-making processes concerning the use of high-dose glucocorticoids in clinical practice and cost reimbursement.

## Discussion

There is an unmet medical need for an effective medical therapy of ISSHL. In this RCT we investigate the efficacy (improvement in hearing) and safety (especially systemic side effects) of high-dose steroids versus standard of care (standard-dose systemic steroids) for the treatment of unilateral ISSHL, when given as a primary therapy. However, there are several challenges associated with RCTs on ISSHL. Since systemic moderate doses of glucocorticoids for the treatment of ISSHL are considered a “standard of care” in most countries around the world, a placebo arm appears to be neither ethically justified nor practically possible due to patient expectations for treatment (usually with steroids). In addition, there is no international consensus on outcome criteria in ISSHL trials.

Determining a clinically relevant or important change in hearing is challenging. In this clinical trial, we have taken a change in hearing threshold of 10 dB HL to represent the minimally important difference (MID). However, we acknowledge that this may not be universally accepted. The decision to choose 10 dB as an MID was based on the test–retest reliability of pure tone audiometric measurements, on established minimal criteria for improvement in individual patients [16, 38], and on a large RCT on this topic with low bias [32].

The clinical relevance of this MID, however, depends on the degree of initial hearing loss (i.e., moderate, severe, profound hearing loss) and whether the patients had serviceable hearing before and/or after therapy [38]. For example, a 10-dB change might not be useful in severe or profound hearing loss if the patient (or the ear) would remain at a cochlear implant candidate level after therapy. The U.S. clinical practise guideline therefore correctly recommends that future studies should report the number of patients reaching serviceable hearing: “… For ears that were rendered nonserviceable by the episode of SSNHL, return to serviceable hearing should be considered a significant improvement, and whether or not this level of recovery occurs should be recorded. Recovery to a serviceable level typically indicates that after recovery, the ear would be a candidate for traditional hearing amplification. Recovery to less than serviceable levels indicates an ear that would in most circumstances not benefit from traditional amplification. For ears with SSNHL to hearing levels that are still in the serviceable range, a 10 dB HL improvement in pure-tone thresholds (the smallest recordable improvement outside of the range of error for most audiograms) or an improvement in WRS of ≥ 10% (approximate lower limit for a statistically significant change based on binomial tables for WRS of > 50% at baseline) should be considered partial recovery and recorded …” (cited from [38]).

Speech audiometry in quiet and noise is preferable over pure tone threshold measurements (or at least as a complementary measure) since they represent communication capabilities better. In German-speaking countries, speech recognition in quiet is typically measured at fixed sound pressure levels including 65 dB SPL (monosyllable word recognition at 65 dB SPL: WRS_65_). At approximately this level, every-day conversation takes place. Since this method is not adaptive to the speech reception threshold (SRT), e.g., such as a “40-dB above speech reception threshold” measure (40 dB SL as recommended by Gurgel et al., 2012, [16]), it allows for a direct assessment of communication abilities and is therefore included in the trial protocol as a secondary outcome measure. The maximum word recognition score (WRS_max_) would also be of interest for the assessment of options and audiological indications for hearing rehabilitation (e.g., conventional hearing aids or cochlear implants). However, the trial population involves patients with an acute “inner ear event.” Therefore, speech audiometry at high levels to determine the WRS_max_ was considered not appropriate and thus not included as an outcome measure. Speech perception in noise can, for instance, be measured in matrix tests that are already available in many languages. These tests, however, are rather time consuming and therefore less practical in the setting of the treatment of an acute event. In addition, they are not available in all study centers. Speech audiometry in noise was therefore not included as an outcome measure in this RCT.

This is the English version for journal publication according to the SPIRIT guidelines based on the full final study protocol (Version: 03 Final, September 1, 2017) available in German language. Some information (e.g., epidemiological data and background information) was updated in the introduction section of this manuscript.

Patient recruitment was stopped on March 27, 2020, due to the COVID-19 pandemic shortly before the planned number of patients was reached. The main reasons for stopping patient recruitment were (1) the (at that time) unknown effect of high-dose systemic glucocorticoid therapy on the course of an infection with the severe acute respiratory syndrome coronavirus type 2 (SARS-CoV-2), (2) the reduction of patient contacts to absolutely necessary medical and surgical treatments during the pandemic, (3) the expected difficulties in appropriate monitoring and quality control due to the restrictions in mobility, and (4) the very small number of remaining patients to complete the trial as planned (325 of 329 patients were already enrolled, with 17 patients with a vestibular schwannoma excluded). The coordinating/chief investigator and the sponsor made the final decision about the termination of patient recruitment after consultation with the DSMB, the deputy coordinating investigator, and the trial statistician. Despite the premature stop, the recruitment of the study can be considered successfully completed with 99% of the required patients.

